6.65 Determination of alpha-tocopherol in serum

**7.0 Statistical Analysis**

**8.0 References**

# 1.0 Aim

The aim of the project is to investigate the relationship between dose and form of selenium and immune function, and to identify functional markers of selenium status.

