# 2.0 Scientific Background

Selenium is involved in the maintenance of antioxidant defence systems and immune function. Although approximately 30 selenoproteins have been identified and more than half characterised, none is a universally accepted functional marker for selenium status. At present, dietary requirements for selenium are based on intakes that maximise activity of the selenoenzyme GPx (Standing Committee on the Evaluation of Dietary Reference Intakes, 2000) but there is considerable debate as to the appropriateness of this endpoint. In addition, dietary recommendations are now focussed on optimal health,not just preventing deficiency disorders, which requires a greater understanding of the reported effects of supra-nutritional intakes of selenium, the relative merits of different forms of selenium, and the impact of marginal selenium status on immune function (Clark et al, 1996; Yoshizawa et al, 1998). The consequences of lower selenium status are not entirely clear, however experimental models have shown that marginal deficiency can affect components of the immune system resulting in general immunosuppression and susceptibility to some cancers and viral diseases (McKenzie et al, 1998; Finch & Turner, 1996; Taylor, 1995); Overt selenium deficiency is associated with dilated cardiomyopathy, skeletal muscle myopathy, osteoarthropathy and cretinism in iodine deficient population (Rayman, 1997; 2000).

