The project will consist of a placebo controlled selenium supplementation study and a dietary intervention with un-enriched and selenium enriched onions. In a parallel group design, subjects will be given either one of three doses of Se-yeast (50, 100 or 200μg selenium/day) or a placebo per day or selenium enriched or un-enriched onions (in the form of test meals) for 12 weeks (Figure 1). The study will allow us to investigate the effects of increasing the intake of dietary selenium as SeMet (found in the tablets) or SeMC (which will be the predominant form in the onions). Selenium supplementation studies using selenite have shown that 50 or 100μg/day selenium significantly increased plasma selenium concentration over a period of 6 weeks, at which point a plateau is reached (Broome et al, 2004). However, the intervention will be carried on for longer because we expect the response from Se-yeast to take longer. Outcome measures will include cellular and humoral immune responses to influenza vaccine (looking at the magnitude and the quality of this response; the up regulation of the immune response may or may not be related to viral clearance, as we are using a killed virus, but this will not be addressed in this study), changes in serum/plasma selenium concentration, selected selenoproteins, and expression of selenium -responsive genes and associated proteins. At IFR, we are currently investigating the effect of selenium form and dose on global gene expression in cell culture studies (micro array data), and have identified several selenium -responsive genes; quantitative RT-PCR (Taqman) analysis of mRNA from one gene (selenoprotein W1) demonstrated a linear dose-response within the physiological range of selenium ([name], unpublished). Results from our cell culture studies will indicate which genes and proteins to investigate in the human intervention study.

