# 3.0 Objectives

- To examine the effect of two different organic forms of selenium that are naturally found in the diet, one of which (SeMC) is purported to confer protection against cancer.
- To provide evidence for a beneficial effect of increasing selenium intake in adults with regard to resistance to influenza virus.
- To investigate the regulation of selenium-responsive genes and protein expression in response to dietary selenium.

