In order to allow for the unlikely possibility of a year effect the control group and each of the three selenium supplementation groups will be evenly and randomly spread over the three years. Unfortunately due to time constraints, this is not possible with the onion groups which will be evenly and randomly spread over only two of the years (i.e. half in each year). The two onion groups will also be able to be analysed separately, but with a reduced power of 18 subjects per group gives a power of 80% of detecting a difference in response variable of 1 standard deviation. This is quite a large effect of the enriched onions, given that they are only “equivalent” to a selenium dose of 50µg/day. This is based on a 25% drop out rate expected for the onion intervention study.

The data would be initially analysed using an ANOVA model to test for differences in end-points between the groups. If the required data assumptions for this model are not met (e.g. normality), then data transformations and/or non-parametric methods will be employed. A repeated measures analysis using all 5 data points per subject will also be used, although it is the end-point (week 12) that is of primary interest.

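### The stated analyses compare groups only; nothing uses dose order or relates a candidate marker to plasma selenium, although identifying markers of selenium status is half of the aim

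*Protocol*

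**What the plan says.** The aim (Protocol 1.0) reads "to investigate the relationship between dose and form of selenium and immune function, and to identify functional markers of selenium status"; this point concerns its second part. Section 2.0 gives the reason. Of the known selenoproteins, "none is a universally accepted functional marker for selenium status". The background then describes current practice, in which "dietary requirements for selenium are based on intakes that maximise activity of the selenoenzyme GPx", and the protocol reports debate about whether that is an appropriate endpoint. The same section contrasts this with selenoprotein W1 mRNA, which in the sponsor's cell culture work "demonstrated a linear dose-response within the physiological range of selenium". The nearest listed objective (3.0) is "To investigate the regulation of selenium-responsive genes and protein expression in response to dietary selenium".

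On analysis, section 7.0 says "The data would be initially analysed using an ANOVA model to test for differences in end-points between the groups". If the assumptions fail, "data transformations and/or non-parametric methods will be employed". It adds a repeated measures analysis of all five time points and names week 12 as the time of primary interest. Proportionality to dose appears in section 7.0 only as an assumption of the power calculation. No section states a contrast between doses, a dose-response model, or a regression or correlation of a candidate marker on plasma selenium.

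**The concern.** By the protocol's own account, the shape of the response matters to the marker question. Section 2.0 sets an enzyme whose activity reaches a maximum beside a transcript that rose linearly with selenium. A significant difference among groups is compatible with either. It shows that something changed with selenium, but not whether the candidate went on changing between 50 and 200 µg/day, or whether it moved with plasma selenium in the people measured.

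What is at stake is the second half of the aim. The candidates are numerous: several GPx activities, thioredoxin reductase, selected proteins, selected genes and a microarray (6.62i). If the results come only as group comparisons, the step from responsive to marker of status would have to be made afterwards, without a stated analysis behind it.

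**Working it through.** **Inputs.** Doses 0, 50, 100 and 200 µg/day; 24 per group, or 18 after 25% drop-out; range of 1 SD; response proportional to dose; two-way ANOVA with a four-level group and a three-level year effect (all section 7.0). Alpha is not stated; 0.05 is assumed.

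**Formula.** With group means μ in SD units and n per group, the noncentrality is λ = n × Σ(μ − mean)². Power is the probability that a noncentral F with 3 and 4n − 4 − 2 degrees of freedom exceeds its 5% critical value. At n = 24 the residual degrees of freedom are 90.

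**The plan's own figure.** Section 7.0 gives 80% for four groups of 24. With the two extreme groups 1 SD apart and the other two midway, Σ = 0.5, λ = 24 × 0.5 = 12.0 and power is 82.2%. The stated figure is met.

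**Two shapes under the same test, n = 24.**
- Proportional, 0/0.25/0.5/1: mean 0.4375, Σ = 0.547, λ = 24 × 0.547 = 13.1, power 85.8%.
- Flat from the lowest dose, 0/h/h/h: Σ = 0.75h². Setting 0.75h² = 0.547 gives h = 0.854, so λ = 13.1 and power is again 85.8%.
- Flat with the same 1 SD range, 0/1/1/1: Σ = 0.75, λ = 18.0, power 95.1%.

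At n = 18 the first two both give 72.6%. With alpha 0.01 or 0.10 (n = 24), the first two both give 66.9% or 91.9%, and the third gives 84.5% or 97.6%. In the six-group ANOVA at 18 per group, with both shapes spanning 1 SD and the onion arms set at 50 and 0 µg/day, the flat marker has 97.4% and the proportional one 77.2%.

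**Analyses that could separate the shapes** (four tablet arms, 1 SD range, one-way residual, n = 18 then n = 24):
- 200 v 50 µg/day for a proportional marker (difference 0.75 SD): 60%, 73%.
- Departure from a straight line for a flat marker (residual sum of squares 0.4, so λ = 7.2 and 9.6): 65%, 78%.
- A linear trend alone does not suffice: at n = 24 a flat marker would still give a significant trend 82% of the time.

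**Are the paired data there?** Section 6.31 divides the 80 mL draw into 3 + 10 + 15 + 12 + 40 mL, and the 40 mL immune portion is omitted at week 6. That leaves 3 + 10 + 15 + 12 = 40 mL, the week-6 volume in section 4.1. Plasma selenium, selenoproteins and RNA are therefore drawn together at weeks 0, 6 and 10, with the week-10 sample taken before the vaccine (6.1). Over the 96 tablet volunteers in Table 1 that is 96 × 3 = 288 pairs if all complete, or 4 × 18 × 3 = 216 with 18 per group.

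**The case against.** Several stronger readings are tempting, and the protocol does not support them.

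- A reader might infer that the ANOVA is the only test and that the week 0, 6 and 10 data go unused. Neither is so: section 7.0 adds a repeated measures analysis of all five points. What is missing is narrower. As described, that analysis still compares groups and does not pair a marker with plasma selenium.
- A reader might infer that the trial cannot tell the shapes apart. That is true of the overall F test only. Four ordered, randomised doses are in the design, and the group means would display a plateau, though no formal comparison is stated.
- A reader might infer that the protocol makes a significant F the definition of a functional marker. It nowhere says so.
- A reader might infer that a plateau disqualifies a marker. Section 2.0 reports debate about the GPx endpoint without giving a reason. It also says that selenomethionine is incorporated non-specifically into proteins, so plasma selenium on Se-yeast need not equal functional supply. A strict rule could reject a useful candidate.

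The equal power above is also by construction, since 0.854 was solved for. It illustrates what the F test is blind to and does not estimate how often this will happen. The comparison at equal 1 SD ranges does not depend on that choice.

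Finally, a separate analysis plan may state these analyses, and the word initially leaves room for more. This stands as a limit on the point. But the protocol itself names the main test and time point, and these do not reach half of its aim.

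**Conclusion.** The point holds as a cheap improvement. The analyses stated in section 7.0 can establish that a candidate is selenium-responsive, which serves the gene and protein objective in section 3.0. They do not by themselves support calling it a marker of selenium status, because neither dose order nor plasma selenium enters them. The F test treats the two shapes alike at equal spread and favours the flat one at equal range (95.1% against 85.8%). These figures assume alpha 0.05, 24 completers in each tablet arm, normal errors with a common SD, and additive year effects balanced across the arms. The blindness of the F test to the pattern of the means does not depend on them.

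**What to change.** Add to section 7.0, for each candidate marker in the four tablet arms:

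1. A linear trend across 0, 50, 100 and 200 µg/day with a test of departure from linearity, and the 200 v 50 µg/day difference with its confidence interval.
2. A mixed model of the marker on same-visit plasma selenium at weeks 0, 6 and 10, with volunteer and visit effects. Using only these weeks keeps the response to vaccination out of the relation, which matters because the possible genes in 6.62i include immune genes such as IL10 and CD1D. The visit effect keeps drift over the ten weeks out of the slope.

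Report the shape with its uncertainty, and do not apply a pass/fail rule that a marker must show no plateau. At 60-78% power, finding no plateau would often mean only that it was not detected. Examine the onion pair separately, because section 2.0 says that the two forms of selenium are metabolised differently.

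The cost is a paragraph of protocol text and a little more analysis. No extra samples, visits or volunteers are needed. The remaining limitation is the moderate power to separate the shapes, which the confidence intervals will make visible.

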# 2.0 Scientific Background

Selenium is involved in the maintenance of antioxidant defence systems and immune function. Although approximately 30 selenoproteins have been identified and more than half characterised, none is a universally accepted functional marker for selenium status. At present, dietary requirements for selenium are based on intakes that maximise activity of the selenoenzyme GPx (Standing Committee on the Evaluation of Dietary Reference Intakes, 2000) but there is considerable debate as to the appropriateness of this endpoint. In addition, dietary recommendations are now focussed on optimal health,not just preventing deficiency disorders, which requires a greater understanding of the reported effects of supra-nutritional intakes of selenium, the relative merits of different forms of selenium, and the impact of marginal selenium status on immune function (Clark et al, 1996; Yoshizawa et al, 1998). The consequences of lower selenium status are not entirely clear, however experimental models have shown that marginal deficiency can affect components of the immune system resulting in general immunosuppression and susceptibility to some cancers and viral diseases (McKenzie et al, 1998; Finch & Turner, 1996; Taylor, 1995); Overt selenium deficiency is associated with dilated cardiomyopathy, skeletal muscle myopathy, osteoarthropathy and cretinism in iodine deficient population (Rayman, 1997; 2000).

Dietary selenium is mainly present in organic complexes, such as selenomethionine (SeMet) found in cereals and plant foods, and Se- methylselenocysteine (SeMC) in selenium -accumulator plants such as onions and brassica vegetables, with smaller quantities of inorganic selenium derived from animal-based foods and dietary supplements (Combs, 2001). The metabolism and bioactivity of selenium is dependent on its chemical form: inorganic selenium can be used directly for the synthesis of GPx and other selenoproteins whereas selenomethionine is initially incorporated into tissue proteins, and only released for selenoprotein synthesis after further metabolism to selenide and selenocysteine (Reilly, 1996). The bioactivity of dietary selenium is related to its chemical form; SeMC has been identified as the most potent form of selenium in terms of protection against cancer possibly because, unlike SeMet which is incorporated non-specifically into proteins (Whanger, 2004), it can be converted directly into methyl selenol (Ca et al, 1995), a bioactive substance associated with cancer prevention (Ip & Ganther, 1996).

Recent epidemiological data from a pooled analysis of three clinical trials showed that individuals whose blood selenium values were in the highest quartile had a statistically significant lower risk (OR=0.66) of developing a colorectal adenoma (a pre-cancerous lesion) compared with individuals in the lowest quartile. These studies, therefore, suggest a mechanism for the decreased risk of colon cancer with selenium in which aberrant, age-related CpG island methylation is decreased by the inhibition of DNMT expression and activity. This study gives a unique opportunity to investigate the effect of selenium supplementation using recently developed techniques for the sensitive and accurate quantification of CpG island methylation in exfoliated colon cells present in faeces.

Intakes of selenium in the UK have fallen from a mean of 60μg/day in 1974 to 30-40μg/day in recent years (Ysart et al, 1999) mainly due to the replacement of Canadian wheat (high in selenium) with European wheat (low in selenium); this has resulted in a fall in the mean plasma selenium concentration (Rayman, 1997). One of the proposed consequences of marginal selenium status is impaired immune function. As people age, they are more prone to infections and tumours and this is, at least in part, related to a decline in immune function. One effect of ageing on T lymphocytes is a shift towards a T-helper 2 (Th2) response during an infection, which means a reduced production of Th1 cytokines such as interleukin-2 (IL-2) and interferon-gamma (IFN-) (Cakman et al, 1996). In addition, natural killer (NK) cells, responsible for recognising and killing tumour and virally infected cells, exhibit an age-associated decline in activity, particularly in their ability to proliferate and to kill NK-resistant cell lines in response to IL-2 stimulation (Solano et al, 1999). As a direct consequence of this age-related decline of immune effectiveness, infectious diseases remain a significant cause of morbidity and mortality in the elderly. In particular, influenza virus is a globally very important contagion for the elderly (Nicholson et al, 2003) and few other diseases exert such huge toll in terms of suffering, medical consultation, hospital admission and economic loss (CDC-USA, 2003; Thompson et al, 2003).

Selenium supplementation increased antibody titre response to influenza vaccine in elderly individuals (Girodon et al, 1999), whereas other micronutrients (β-carotene, retinol, α-tocopherol and zinc) had no effect on the immune response to influenza vaccine (Gardner et al, 2000). At IFR data has recently been produced indicating beneficial up-regulation of an additional immune function response by selenium ([name], unpublished). It was initially observed that short-term *in vitro* culture of human PBL with selenium, followed by challenge with influenza virus, dramatically increased the number of CD3+ CD8+ cytotoxic T cells that contain granzymes and perforins granules. This indicates an increase in cell-mediated immunity which is an important defence against viral attack. Secondly, it was found that there was an up-regulation of IFN-2, a major player in the anti-viral response. Interestingly, it was also noticed that there was an increase in production of IL-13, important for antibody production (Bajer et al, 2003), by CD3+ CD4+ T helper cells. Although these results were observed when both selenomethionine and SeMC were used, it seems that the latter is a more potent stimulator of immune response. These data clearly show the potential of selenium to improve both humoral and cellular immunity. Establishing the potential role of selenium as an enhancer of immune response in vivo may provide an evidence-base for public health policy, with important consequences for preventing influenza and similar diseases in the elderly.

The project will consist of a placebo controlled selenium supplementation study and a dietary intervention with un-enriched and selenium enriched onions. In a parallel group design, subjects will be given either one of three doses of Se-yeast (50, 100 or 200μg selenium/day) or a placebo per day or selenium enriched or un-enriched onions (in the form of test meals) for 12 weeks (Figure 1). The study will allow us to investigate the effects of increasing the intake of dietary selenium as SeMet (found in the tablets) or SeMC (which will be the predominant form in the onions). Selenium supplementation studies using selenite have shown that 50 or 100μg/day selenium significantly increased plasma selenium concentration over a period of 6 weeks, at which point a plateau is reached (Broome et al, 2004). However, the intervention will be carried on for longer because we expect the response from Se-yeast to take longer. Outcome measures will include cellular and humoral immune responses to influenza vaccine (looking at the magnitude and the quality of this response; the up regulation of the immune response may or may not be related to viral clearance, as we are using a killed virus, but this will not be addressed in this study), changes in serum/plasma selenium concentration, selected selenoproteins, and expression of selenium -responsive genes and associated proteins. At IFR, we are currently investigating the effect of selenium form and dose on global gene expression in cell culture studies (micro array data), and have identified several selenium -responsive genes; quantitative RT-PCR (Taqman) analysis of mRNA from one gene (selenoprotein W1) demonstrated a linear dose-response within the physiological range of selenium ([name], unpublished). Results from our cell culture studies will indicate which genes and proteins to investigate in the human intervention study.

# 3.0 Objectives

- To examine the effect of two different organic forms of selenium that are naturally found in the diet, one of which (SeMC) is purported to confer protection against cancer.
- To provide evidence for a beneficial effect of increasing selenium intake in adults with regard to resistance to influenza virus.
- To investigate the regulation of selenium-responsive genes and protein expression in response to dietary selenium.

# 4.0 Study Design

## 4.1 Overview

A 12 week intervention will be carried out in which 6 groups of 50-64y old men and women (n=24 per group) with low plasma (or serum) selenium are fed one of three doses of selenium (50, 100 or 200µg/d) as selenium enriched yeast (Se-yeast) tablet, a placebo tablet, selenium-enriched onions (equivalent to 50µg/day selenium) or un-enriched onions during the summer, autumn and winter periods (July-February). Subjects will be given an influenza viral challenge 10 weeks after starting the intervention. Volunteers will be informed that our study also vaccinates during the months December to February which is outside the traditional flu vaccination period adopted by the NHS. The precise time of vaccination for the volunteers will depend on their intervention starting date and may therefore take place in the period between December to February. Health care workers and those who are offered free flu vaccination from the NHS will not be eligible to take part in the study during the months of December to February.

The Se-yeast treatment will take place over 3 years; the onion treatment will take place during years 2 and 3 (the onions will be grown in years 1 and 2 for consumption the following year). The onions will be stored for a number of months and then incorporated into meals which will be stored at -18°C until required.

The control subjects will take a placebo and undergo the same tests. Venous blood samples will be taken pre-vaccination at baseline (week 0, 80mls), 6 (40mls) and 10 weeks (80mls) then post vaccination at 11 (80mls) and 12 weeks (80mls). Saliva samples will be obtained at baseline (pre-vaccination) and 12 weeks (post-vaccination). Blood samples will be used for the assessment of plasma selenium concentration (Q-ICPMS), plasma vitamin E (HPLC), selected selenoproteins, selenium-responsive genes, protein expression, and cellular and humoral immune response. The saliva samples will be tested for antibody titres to influenza antigens. A 24hour urine collection will be made during week 6 to determine selenium concentration.

Week 0

6

10

11

12

[figure not shown]

Up to 5 onion based test meals consumed

per week for 12 weeks

[figure not shown]

-Se

+Se

1 capsule taken every day for 12 weeks

Fasted Blood sample (60mL)

24hour urine collection

Influenza virus vaccination

Volunteer groups taking part in study

Saliva sample

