Uncertainty about delivery dates for flu vaccines cause logistical problems. We cannot delay the supplement/dietary intervention until we have confirmation of the delivery date of the flu vaccine. We also need to achieve a continuous flux of volunteers as we are limited to the number of immune function assays we can manage per week. In each project year the first volunteers start the intervention in July so that week 10 (vaccination) falls into the second half of September a date that was originally be considered feasible for the flu vaccine to be available after having contacted several suppliers. However, a delay in flu vaccine deliveries is a possibility and our suggestion is to allow for some flexibility if this happens. We suggest that volunteers that reach week 10 may continue with supplement/onion meals for a maximum of 3 more weeks if the flu vaccine is not available. If the flu vaccine is still not available at week 13 then a final blood sample will be taken for biomarker and immune function analysis. This approach still allows us to complete our measurements of selenium biomarkers but is less likely to show any effect with respect to immune function. However, this should only affect a limited number of volunteers. How many is difficult to predict as we don’t know for some time when the flu vaccine will be available. We feel that this approach is an acceptable solution as we will still meet all the objectives related to plasma selenium status and biomarkers of selenium status.

**Further, we also suggest extending the current flu vaccination period (September to February) to include March and April 2007 and 2008. We will always endeavour to not vaccinate in March and April but we are dependent on the actual flu vaccine delivery for the life time of this project. The HRGC protocol (Annex 1) and volunteer information (Annex 4) have been amended accordingly.**

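### The stated six-group week-12 ANOVA has no calendar term although vaccination date follows start date across the season; adding year and start period is nearly free, and the stated periods need reconciling

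*Protocol*

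**What the plan says.** **Timing.** Protocol Section 4.1 describes feeding "un-enriched onions during the summer, autumn and winter periods (July-February". Vaccination is at week 10, so its date follows the start date; Section 4.1 says "The precise time of vaccination for the volunteers will depend on their intervention starting date and may therefore take place in the period" December to February. Section 6.1 (text after Figure 2) says "the first volunteers start the intervention in July so that week 10 (vaccination) falls into the second half of September". The same section proposes "extending the current flu vaccination period (September to February) to include March and April 2007 and 2008" and adds: "We will always endeavour to not vaccinate in March and April but we are dependent on the actual flu vaccine delivery". It allows at most three extra weeks on treatment while vaccine is awaited.

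**Eligibility.** Section 4.1 states "Health care workers and those who are offered free flu vaccination from the NHS will not be eligible to take part in the study" in December to February. Section 5.2 excludes people offered free vaccination for a medical condition with no calendar limit. It excludes healthcare workers only when their study vaccination would fall outside July to December.

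**Allocation.** Section 6.4 randomises among four groups in year 1 and six in years 2 and 3 (four for volunteers who dislike onions, Section 6.0), stratified by sex.

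**Analysis.** Section 7.0 plans an initial ANOVA on group, with week 12 of primary interest, and a repeated measures analysis of all five time points. Its one calendar term is a three-level year effect in a two-way model of the four tablet groups, kept for what the section treats as an improbable case. The even spread of those groups over the years is introduced with "In order to allow for the unlikely possibility of a year effect".

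**The concern.** Within one project year, a July starter is vaccinated in September and a late starter in midwinter or, if the fallback is used, in spring. The late starter spends the ten weeks before vaccination in the colder months, when exposure to circulating influenza could move the same antibody and T-cell readouts. The eligible population may also shift around December.

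If the immune end-points vary with calendar time, a model with group alone leaves that variation in the error term. In the six-group model it can also enter the onion-tablet contrast, which bears on the first objective in Section 3.0 (two organic forms of selenium). Start date is known before allocation, so the plan can remove this variation with data it already holds.

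**Working it through.** **1. Dates.** Week 10 is day 70 and the last sample is 14 days later (ignoring the ±2-day margin).
- Vaccination on 28 February 2007 puts the last sample on 14 March, already past the July-February period in Section 4.1.
- Vaccination on 30 April 2007 means a start on 19 February (70 days earlier), or 29 January with the three-week extension (91 days), and a last sample on 14 May.
- A planned vaccination on 1 December 2006 corresponds to a start on 22 September.

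**2. The plan's own power.** Section 7.0 gives 80% for six groups at 18 each, a range of 1 SD and effects proportional to dose. Alpha is not stated; 0.05 is assumed. The means are 0, 0.25, 0.5 and 1 SD for placebo, 50, 100 and 200 µg, 0.25 for enriched onions and 0 for un-enriched onions. Their average is 0.333 and the sum of squared deviations is 0.708. The noncentrality is 18 × 0.708 = 12.75 on 5 and 102 degrees of freedom, so power is 77.2%. At 24 per group it is 89.7%.

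**3. Precision lost.** The protocol gives no seasonal effect size and no late share, so both are assumptions: a share p is vaccinated late, which shifts the response by d SD. The seasonal share of variance is p(1−p)d².
- p = 0.3, d = 0.5: 0.3 × 0.7 × 0.25 = 0.0525.
- p = 0.5, d = 1: 0.5 × 0.5 × 1 = 0.25.

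If the plan's SD already contains this variation, adjusting divides the noncentrality's variance by (1 − share). Power rises from 77.2% to 79.7% in the first case and 89.2% in the second. Spending six degrees of freedom (102 to 96) gives 79.6% and 89.1%, so the cost is under 0.2 points.

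If seasonal variation instead comes on top of the plan's SD, leaving it out lowers 77.2% to 74.2-75.0% for d = 0.5, and to 66.0-68.6% for d = 1 (p = 0.25 to 0.5).

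**4. Bias among concurrently randomised groups.** With season random with respect to group (half late, 1 SD shift, 20,000 simulated trials), type I error is 0.048 for six groups of 18 and 0.050 for four groups of 24: nominal. Chance imbalance remains. The difference in late share between two groups of 18 has SD √(2p(1−p)/18) = 0.144 (p = 0.25) to 0.167 (p = 0.5). Times d = 0.25 to 1, this typically shifts a contrast by 0.04 to 0.17 SD.

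**5. Onion versus tablet.** March-April vaccination is possible only in years 2 and 3. Onion groups run only in those years; tablet groups have two thirds of their volunteers there (Table 1: 32 in each of three years). If a share q of year 2-3 volunteers is vaccinated in March-April, the imbalance is q − (2/3)q = q/3 and the offset is d × q/3. For q = 0.25 and d = 0.5 to 1 this is 0.04 to 0.08 SD. Over q = 0.1 to 0.5 and d = 0.25 to 1 it runs from 0.008 to 0.167 SD. For scale, proportionality gives 50 µg/day an effect of 50/200 = 0.25 SD, and a two-group contrast at 18 each has a standard error of √(2/18) = 0.33 SD.

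**6. Eligibility texts side by side.** A healthcare worker due for vaccination in December is barred by Section 4.1 and admitted by Section 5.2. One due in March or April is outside the months that Section 4.1 lists but excluded by Section 5.2.

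**The case against.** The strongest objection is that covariates are commonly left to a SAP, which is not at hand, and that Section 7.0 calls the ANOVA only the initial analysis. That stands against treating the missing covariate as an error. It does not remove the point: the protocol itself chose a calendar term, limited it to a fallback without the onion groups, and fixed sex as the stratifier, while its own schedule creates variation within the year.

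Second, Section 7.0 already recognises that a year effect could compromise the onion groups and allows them to be analysed separately. This is fair, and the onion-tablet offset is a between-year difference that a year term alone would remove. But the fallback drops the onion-tablet comparison instead of adjusting it.

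A reader might infer three stronger things that the documents do not support.
- That season biases every group comparison. Concurrent randomisation within year rules out systematic bias among the tablet groups and between the onion groups.
- That vaccination routinely runs to April. March and April are a delivery contingency that the team intends to avoid.
- That natural infection would simply be counted as vaccine response. Blood for immune assays is taken at weeks 0 and 10, before vaccination, and repeated measures are planned. The worry applies to an unadjusted week-12 comparison, and more to saliva, which is collected only at weeks 0 and 12.

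Nor is a large change in case mix shown. Section 5.2 excludes people offered free vaccination for a medical condition all year, so the shift may concern healthcare workers only, and their number is not given.

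**Conclusion.** The point holds as an inexpensive improvement to the stated model plus a reconciliation of the text, not as a threat to the validity of the main comparisons. Among tablet groups, and between the onion groups, the cost of omitting calendar time is lost precision and chance imbalance. For onion versus tablet a systematic offset is possible, probably small beside the contrast's standard error.

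The power gain is conditional: about 2.5 points if 5% of the variance is seasonal, and 12 points only in the extreme assumed case of 25%. All seasonal shifts and late shares are assumptions, and alpha is taken as 0.05. The power figures also ignore the slight loss from onion groups being absent in year 1. The conflicts over study period and healthcare-worker eligibility rest on the text alone.

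**What to change.** 1. In the six-group models for immune outcomes, include project year and a start-date period, for example planned vaccination before or from 1 December. Define the period from the start date, not the actual vaccination date, so that it is fixed before allocation.
2. Adjust for the week-0 value of the same immune measure.
3. Do not exclude volunteers whose titre rose between weeks 0 and 10. That selects on a post-randomisation variable which selenium may itself affect. At most, describe such rises by group.
4. Reconcile the period in Section 4.1 with the vaccination window in Section 6.1, and the healthcare-worker rule from December onward in Section 4.1 with that in Section 5.2. Which version is intended is for the sponsor to state.

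**Cost.** Year takes 2 degrees of freedom, period 1 and their interaction 2, so up to 5, plus 1 for baseline: 102 residual degrees of freedom become 96 at 18 per group. Start dates and week-0 blood and saliva are already collected; no new visit or sample is needed.
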